## Abstract

**Objectives:**

AO Spine REsearch objectives and Common Data Elements for Degenerative Cervical Myelopathy [RECODE-DCM] is a multi-stakeholder consensus process aiming to promote research efficiency in DCM. It aims to establish the top 10 research uncertainties, through a James Lind Alliance Priority Setting Partnership [PSP]. Through a consensus process, research questions are generated and ranked. The inclusion of people with cervical myelopathy [PwCM] is central to the process. We hypothesized that presenting PwCM experience through word cloud generation would stimulate other key stakeholders to generate research questions better aligned with PwCM needs. This protocol outlines our plans to evaluate this as a nested methodological study within our PSP.

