## Introduction

Degenerative cervical myelopathy [DCM] is the most common cause of spinal cord dysfunction worldwide [1]. It arises when arthritic changes in the cervical spine lead to its narrowing - causing compression injury to the cervical spinal cord. Currently, despite the best available treatment [2], many people with DCM will be left with life-changing disabilities [3] and some of the worst quality of life scores of chronic diseases [4].

AO Spine REsearch objectives and Common Data Elements for Degenerative Cervical Myelopathy [RECODE-DCM] is a multi-stakeholder consensus process which ultimately aims to accelerate research progress, through the formation of recommendations that improve research efficiency [5]. It combines several consensus initiatives, including to confirm the definition of DCM, to establish the top 10 research uncertainties, and to establish a minimum critical dataset for clinical research, care, and audit.

The process to establish research uncertainties is supported by organizations such as the James Lind Alliance [JLA] [6] as a Priority Setting Partnership [PSP]. JLA methodology starts by seeking research suggestions from patients, family, caregivers, and front-line healthcare professionals. Commonly this has been delivered using an electronic survey, with sub-sections adapted to the condition and scope, to stimulate ideas. For AO Spine RECODE-DCM, it was established that these sub-sections would include diagnosis, treatment, long-term management, and other issues [5].

A major driver of inefficiency in health research is proposed to be the exclusion of end-users (e.g., people with cervical myelopathy [PwCM]) from participation in research design [7, 8]. Their involvement is central to impactful results [9–11]. While this is recognized in the PSP by their participation in the surveys, we hypothesized that their experience could also be used to stimulate other stakeholders to generate research questions aligned with this user group. Their input should be helpful as one of the challenges for a DCM PSP is that a diversity of healthcare professionals are involved in DCM care, but generally, it forms a minority of their practice or is confined to a short stage of the disease, e.g., diagnosis [12, 13]. This lack of information and the narrow foci of each practitioner’s role have been proposed to hamper modern clinical research creativity [14].

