## Methods

The word clouds were generated working with Myelopathy Support, an online peer-to-peer support community for individuals with DCM and their caregivers. Ethical approval has not been required for the involvement of the Myelopathy Support members as their role is to help to develop the word clouds for the survey and they are not research participants. The moderator for the Myelopathy Support group is a member of the Steering Group for the Priority Setting Partnership who design and manage the survey. Myelopathy Support is an arm of Myelopathy.org, an international charity for DCM. Myelopathy Support includes an online support group hosted on Facebook (California, USA). The group is closed, and access is moderated by Myelopathy.org volunteers [IS]. Individuals wishing to join the group are required to confirm they have myelopathy and will adhere to community guidelines. Prior experience has demonstrated that demographics and disease characteristics of this group, aside from a female gender predominance, are broadly representative of DCM [18–22].

Over a 2-week period, four posts were pinned to the top of the Myelopathy Support group: (1) “What words do you associate with diagnosis phase of myelopathy?” (2) “What words do you associate with the management phase of myelopathy?” (3) “What words do you associate with the long-term care/living with myelopathy?” (4) “Any other relevant words?”. The posts were accompanied by covering information outlining the background and rationale for this exercise, piloted and approved by IS [Supporting Information 1]. In short, group members were encouraged to add their unrepresented suggestions as comments on the particular post or posts and to vote (as likes or with emotions) the posted words with which they agreed. This exercise was moderated by a group administrator [IS]. No data was collected on individual participants, e.g., their demographics. There was no limit on how many times a group member could contribute.

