## Implementation plan for AO Spine RECODE-DCM

AO Spine RECODE-DCM includes several parallel consensus processes, including a research priority setting partnership and the development of a minimum data set. The AO Spine RECODE-DCM survey will be accessed via a single-entry point, with block randomization to one of the two streams (either Priority Setting Partnership or Minimum Data Set) per stakeholder group (spinal surgeon, other healthcare professionals, persons with DCM and their supporters). This methodology was chosen for efficiency to enable a single recruitment phase. Further detail on the overall process is provided in reference [5].

For participants allocated to the PSP, further 1:1 block randomization will occur to two streams, a survey including word clouds and a second stream without word clouds. For those allocated to the word cloud stream, participants will complete the survey as planned initially. However, after survey completion, respondents will be presented with a brief overview of the development method and aims of the word cloud subproject. Participants will then be presented with each word cloud in turn, with the option to submit further research questions. This approach was taken for two principal reasons. Firstly, to ensure the traditional JLA methodology can be conducted contemporaneously, but still partitioned if required, and secondly, to enable any cross over of responses within the word cloud arm to be considered. Participants will be able to move freely within the survey up until the point they reached a final “thank you” page. Consequently, it will be theoretically possible for participants in the word cloud stream to edit their pre-word cloud form having seen the word clouds. This cannot be tracked by the survey platform. However, by retaining an arm who have no access to the word clouds, any such cross over can be evaluated.

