As part of any JLA PSP, the raw suggestions are processed into their individual questions. Then questions deemed “out of scope” are removed, before the remaining questions are collated into common themes, each represented by a summary question. This process is iterative, with a clear audit trail to track where any submission ends up. Consequently, the overall number of questions submitted, alongside the number deemed “in-scope” research questions and the number linked to a summary question appearing in the final research priority list, will be recorded in this evaluation. These numbers will be compared between streams, and for those in the word cloud stream, before and after viewing the word cloud. Metrics will be evaluated overall and per stakeholder group, as well as specifically for each category of question (diagnosis, treatment, long-term management, and other). The impact of the relative size of a word or its relative competition (the number of other words in the cloud) will also be evaluated, by comparing the number of questions generated that match each word and evaluating for a positive correlation. The use of word clouds will be judged meaningful if they prompt a greater breadth of suggestions across the phases of care. Suitable statistical methods will be used for comparisons based on the distribution of the data.

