## Discussion

Primarily driven by individuals with DCM, word clouds were developed for associations with the diagnosis, treatment, long-term phases of care, and an “other” category. These will be nested within AO Spine RECODE-DCM, in order to evaluate their role in supporting the research uncertainty gathering phase of a JLA Research Priority Setting Partnership.

The diagnosis word cloud highlights prominent symptoms and MRI, the gold standard diagnostic tool. The treatment section highlighted the gold standard treatment—surgical decompression. The long-term management section highlighted disability and tiredness. The other category highlighted ignorance of the condition. Amongst several pervasive themes were pain and psychological consequences such as anxiety and depression.

The perspective of PwCM has been limited within DCM research to date, but wider experience from healthcare shows this can bring critical insights [8]. In one of the few previous DCM examples, our evaluation of PwCM recovery priorities identified that pain, alongside upper and lower limb function, was most valued [18]. This contrasts the current outcomes of research studies not including PwCM input and supports the rationale for AO Spine RECODE-DCM, and its establishment of a minimum data set. The broad range of ideas displayed goes beyond current research foci [23] indicating the value of engaging PwCM in research design [8].

We hypothesize that this PwCM perspective could be enhanced within a JLA PSP. While PSP were developed to ensure the voice of patients is incorporated into setting a research agenda, this is only really considered by the group as a whole during the final consensus meeting. Put specifically, professionals do not have the opportunity to reflect on “patient” perspectives until summary questions have already been generated and shortlisted. In this nested methodological study, we will therefore evaluate whether the PwCM generated word clouds can help the group as a whole develop research questions and specifically, priority research questions.

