We acknowledge that this was an internet-recruited, convenience sample of persons with DCM. Therefore, the generalization of these word clouds, in the absence of demographics, cannot be fully evaluated. Experience from prior research involving this group indicates their demographics and disease characteristics are broadly representative of DCM [18–22]; moreover, the use of such sampling is the mainstay of traditional JLA PSP [29]. As these details will be captured within AO Spine RECODE-DCM, potential bias can be evaluated.

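### The hypothesis is about other stakeholders' alignment with PwCM needs, but the evaluation compares question counts and judges success on breadth, so alignment is not directly tested

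*Protocol article*

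**What the plan says.** **Hypothesis.** The Objectives paragraph of the abstract says that presenting PwCM experience as word clouds "would stimulate other key stakeholders to generate research questions better aligned with PwCM needs". The Introduction repeats it: "their experience could also be used to stimulate other stakeholders to generate research questions aligned with this user group". Both statements name who should change (stakeholders other than PwCM) and what should change (alignment with PwCM).

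**Design.** Under the implementation plan, survey entrants are first block-randomised between the Priority Setting Partnership and the Minimum Data Set, "per stakeholder group (spinal surgeon, other healthcare professionals, persons with DCM and their supporters"). Within the partnership, "further 1:1 block randomization will occur to two streams, a survey including word clouds and a second stream without word clouds".

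**Measures.** The same section records the number of questions submitted, the number in scope, and the number linked to a summary question on the final priority list. These are compared between streams and, in the word cloud stream, before and after viewing. On the analysis sets it says: "Metrics will be evaluated overall and per stakeholder group". Questions are also matched to cloud words, to look for a correlation with word size and with the number of competing words. The stated criterion for a meaningful result is a wider range of suggestions over the phases of care.

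**Aim as restated.** The Discussion says the study will evaluate whether the clouds can "help the group as a whole develop research questions and specifically, priority research questions".

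**Poll contributors.** Methods says of the word polls: "No data was collected on individual participants, e.g., their demographics". The Discussion, after conceding that generalisation cannot be fully evaluated, adds: "As these details will be captured within AO Spine RECODE-DCM, potential bias can be evaluated".

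**The concern.** The claim and the yardstick are different constructs. The hypothesis concerns the content of professionals' questions: whether they move towards what PwCM need. The measures concern how many questions arrive, how many are in scope, how many end up on a jointly agreed list, and how widely they spread. A reader of the final report would expect a verdict on alignment and would receive one on volume and breadth.

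At stake is the interpretation of either outcome. A result that meets the breadth criterion could be reported as support for the hypothesis when alignment was never measured. A result that fails it could hide a real shift of professionals' questions towards PwCM concerns. Because the target population also moves, from other stakeholders to everyone, the article does not say which of the planned results answers the question it poses.

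A second, smaller issue is the assurance about bias in the word clouds. It rests on survey demographics, which describe a different set of people from those who supplied and voted on the words.

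**Working it through.** There is no stated sample size, power, significance level or expected stakeholder mix, so there is no figure to reproduce. The check compares the hypothesis with each planned measure.

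**1. What the hypothesis needs.** A quantity that (a) reflects agreement between a question and PwCM needs, (b) is compared between the randomised streams, and (c) is read in stakeholders other than PwCM.

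**2. Each measure against those needs.**

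| Planned measure | Reflects alignment? | Compared between streams? | Available outside PwCM? |
|---|---|---|---|
| Questions submitted | No, volume | Yes | Yes, per group |
| Questions in scope | No, scope | Yes | Yes, per group |
| Questions linked to the final list | Indirectly: the list reflects all stakeholders and, as described, both streams | Yes | Yes, per group |
| Questions matching cloud words | Nearest proxy | No: planned as a correlation with word size and competition | Not stated |
| Breadth over phases of care (success criterion) | No, spread | Comparison not spelled out | Not stated |

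No row meets all three needs directly. Linkage to the final list comes closest among the stream comparisons. But the article describes a single list, so questions prompted by the clouds can help to form the standard by which they are then scored. Word matching is also not a pure PwCM standard. According to Results, 25 words suggested after internal discussion and consultation joined the 79 words that members had submitted before the second poll.

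**3. Can breadth and alignment separate?** Yes, in both directions. The survey has four categories (diagnosis, treatment, long-term management, other).
- Suppose a surgeon who would have asked only about treatment asks one question in each of the four categories, and none concerns anything PwCM raised. Breadth rises and alignment does not.
- Suppose a surgeon still asks only about treatment, but now about treatment issues that PwCM raised. Alignment rises and breadth does not.

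Meeting the success criterion is therefore neither sufficient nor necessary for the hypothesis.

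**4. Whose questions?** The abstract and Introduction say other stakeholders; the Discussion says the whole group. The plan produces both overall and per-group results but does not say which one tests the hypothesis.

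**5. Bias among poll contributors.** To assess it, one needs characteristics of the contributors, or a way to recognise them among survey respondents. Methods rules out the first. The article describes nothing that provides the second. Survey demographics alone describe survey respondents.

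**The case against.** The best defence has three parts.

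**Results are planned per stakeholder group.** This stands. A reader might infer that because PwCM are pooled into the overall comparison, the question about other stakeholders cannot be answered. The documents do not support that: surgeons and other healthcare professionals are separate groups with their own planned comparisons. Nor can one quote how far pooling dilutes the effect. That needs an assumed share of PwCM and an assumed absence of effect in them, and the article gives neither.

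**Proxies for alignment exist.** This stands in part. PwCM help to shape the final list, the audit trail follows every submission, and word matching is planned. But the list is a joint product, and the matching is not a comparison between streams.

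**A condensed article leaves detail elsewhere.** This stands for detail such as adjustment and strata. A reader might infer that the second randomisation ignores stakeholder group; the article is merely silent, and it refers to another publication for the overall process. It does not excuse a success criterion that differs from the hypothesis, since both are printed here.

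A reader might also infer that PwCM who wrote the cloud words contaminate the no-cloud stream. Overlap is possible but nowhere shown, and randomisation would be expected to spread any such people over both streams. On the bias statement, the survey items are not shown, so a linking item cannot be ruled out; the article, however, gives only the captured details as its ground.

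**Conclusion.** The point holds as a mismatch between hypothesis and evaluation. As written, the plan does not directly test whether clouds bring other stakeholders' questions closer to PwCM needs, and its success criterion can be met or missed independently of that. The data needed will largely exist: professionals can be analysed apart from PwCM, and the audit trail records where each question goes. The gap is in definition, not in design.

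Its size cannot be given as a number, because the article states no sample size, effect or stakeholder mix. The conclusion rests on the article's own wording and on the logical separation of breadth from alignment; it assumes nothing about how PwCM respond to the clouds.

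The statement that bias among poll contributors can be evaluated is not supported by what the article describes, because no individual data were collected on them.

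**What to change.** 1. Name the already planned between-stream comparison in surgeons and other healthcare professionals as the test of the hypothesis. Supporters share a group with persons with DCM, so this test leaves them out; say so.
2. Define an alignment measure from the audit trail, coded blind to stream: the number per randomised respondent, zero if none, of in-scope questions that fall under a summary question also raised by PwCM in the no-cloud stream. Taking the reference from the no-cloud stream keeps cloud-prompted PwCM submissions out of it. Counting per randomised respondent keeps everyone in the comparison. Report the share of in-scope questions as a secondary measure only, since it is undefined for respondents with none and its denominator may itself be changed by the clouds.
3. Keep breadth as a separate outcome. Alternatively, reword the hypothesis so that it matches the breadth criterion and the whole-group aim in the Discussion.
4. Add a yes/no survey item on having taken part in the word polls, so that contributors among the respondents can be described. If that is not possible, withdraw the statement that this bias can be evaluated.

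Cost: wording changes, a little extra coding and at most one survey item. The main test will have fewer respondents than the pooled comparison.

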**Methods:**

An online poll asked PwCM to submit and vote on words associated with aspects of DCM. After review, a refined word list was re-polled for voting and word submission. Word clouds were generated and an implementation plan for AO Spine RECODE-DCM PSP surveys was subsequently developed.

**Results:**

Seventy-nine terms were submitted after the first poll. Eighty-seven refined words were then re-polled (which added a further 39 words). Four word clouds were generated under the categories of diagnosis, management, long-term effects, and other. A 1:1 block randomization protocol to assess word cloud impact on the number and relevance of PSP research questions was generated.

**Conclusions:**

We have shown it is feasible to work with PwCM to generate a tool for the AO Spine RECODE-DCM nested methodological study. Once the survey stage is completed, we will be able to evaluate the impact of the word clouds. Further research will be needed to assess the value of any impact in terms of stimulating a more creative research agenda.

**Supplementary Information:**

The online version contains supplementary material available at 10.1186/s13063-021-05349-8.

## Introduction

Degenerative cervical myelopathy [DCM] is the most common cause of spinal cord dysfunction worldwide [1]. It arises when arthritic changes in the cervical spine lead to its narrowing - causing compression injury to the cervical spinal cord. Currently, despite the best available treatment [2], many people with DCM will be left with life-changing disabilities [3] and some of the worst quality of life scores of chronic diseases [4].

AO Spine REsearch objectives and Common Data Elements for Degenerative Cervical Myelopathy [RECODE-DCM] is a multi-stakeholder consensus process which ultimately aims to accelerate research progress, through the formation of recommendations that improve research efficiency [5]. It combines several consensus initiatives, including to confirm the definition of DCM, to establish the top 10 research uncertainties, and to establish a minimum critical dataset for clinical research, care, and audit.

The process to establish research uncertainties is supported by organizations such as the James Lind Alliance [JLA] [6] as a Priority Setting Partnership [PSP]. JLA methodology starts by seeking research suggestions from patients, family, caregivers, and front-line healthcare professionals. Commonly this has been delivered using an electronic survey, with sub-sections adapted to the condition and scope, to stimulate ideas. For AO Spine RECODE-DCM, it was established that these sub-sections would include diagnosis, treatment, long-term management, and other issues [5].

A major driver of inefficiency in health research is proposed to be the exclusion of end-users (e.g., people with cervical myelopathy [PwCM]) from participation in research design [7, 8]. Their involvement is central to impactful results [9–11]. While this is recognized in the PSP by their participation in the surveys, we hypothesized that their experience could also be used to stimulate other stakeholders to generate research questions aligned with this user group. Their input should be helpful as one of the challenges for a DCM PSP is that a diversity of healthcare professionals are involved in DCM care, but generally, it forms a minority of their practice or is confined to a short stage of the disease, e.g., diagnosis [12, 13]. This lack of information and the narrow foci of each practitioner’s role have been proposed to hamper modern clinical research creativity [14].

Word clouds are a tool which enables qualitative data to be displayed; the importance or frequency is assigned by word size or orientation. In the medical literature, word clouds are mainly used to report qualitative patient interview data [15], although further afield they have been used to stimulate creativity [16, 17].

This article describes the generation of word clouds of terms suggested by individuals with DCM, for diagnosis, treatment, long-term management, and other aspects of DCM, so that they can be used in the PSP survey. The article also outlines how word clouds will be nested within AO Spine RECODE-DCM, in order to evaluate their impact on responses in the online survey. This will give insight into their role and value to stimulate a creative research agenda from respondents to surveys about research priorities.

